### Outcome measures

#### Primary outcome

Mean number of alters who returned photo verified syphilis testing results per index in each arm, including facility-based test and self-testing in 3 months.

#### Secondary outcomes

1) Proportion of first-time syphilis testing among participants; 2) Proportion of testers with a positive syphilis testing result; 3) Economic evaluation in terms of total cost of implementing each of the three arms, the average cost per tester, the average cost per syphilis diagnosis, and the incremental cost-effectiveness ratio for the three arms; 4) Adverse events during the delivery procedures in each arm; 5) Mean number of alters who received the test kit; 6) Proportion of repeat testing among indexes and alters in each arm.

### Data collection

#### Syphilis testing record and results

All indexes’ information will be recorded using online surveys (Wenjuanxing online survey platform). Alters can photograph and upload their testing results to an online social media platform “WeChat” (instant messaging service/application) by scanning the QR code in the result report card. Syphilis testing results can be either from facility-based testing or self-testing.

### Surveys

#### Baseline survey for index

All eligible indexes will complete a baseline survey online on the web-based survey platform Wenjuanxing (Changsha Haoxing Information Technology Co., Ltd., China) at enrollment. The baseline survey collects information on socio-demographic information, history of sexual behaviors, syphilis testing, HIV testing and other STIs testing, and their social network. Sociodemographic information includes age, biological sex, residence status, marital status, highest education, monthly income, sexual orientation, and whether they disclosed their sexual orientation with others. Sexual behaviors include sexual history with men and/or women, role during sex with men, condom use, type of sex partners, group sex, and drug use. Facility-based testing or self-testing history of syphilis, HIV and other STIs, and treatment experience will also be collected. A set of questions including a scale to measure social support, community leadership, and the size of their social network will be asked [24, 25].

#### Alter survey

Each alter in the three arms will receive an online survey link after uploading their syphilis test results. The survey will be created on the Wenjuanxing platform and includes questions on the relationship between the indexes and the alters, sociodemographic information, sexual behavior, the experience of receiving syphilis testing packages or links, testing history of syphilis, HIV and other STIs, and social network. The experience of accepting syphilis testing packages or links includes the behavior of the indexes when delivering syphilis testing packages or links, and the satisfaction to the delivery process of syphilis testing packages or links. Adverse events will be asked to identify whether the alters were being forced to test, have received physical and/or verbal abuse, or being misunderstood from indexes etc. during the delivery procedures.

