#### Referral link SST delivery arm

Index MSM in this arm will initially receive a unique SST referral link, which can be shared with up to three alters after baseline survey. Each link will expire after three times of usage. Each alter can only apply for one SST package with the link, which can be accessed by only one device (both a Wechat account and a phone number). Further, the SST package will be posted to the alter free of charge (free express delivery).

In all three study arms, each package or link will be assigned with a unique number for future returned results tracking and index matching. Alters will receive 3 USD when they send a photo verification of their self-testing or facility-testing results and complete the alter survey. Their matching index will also receive an extra 3 USD as incentive of successful distribution. In addition, each index can apply for additional three packages (refundable 3 USD deposit for each SST package; free of charge for notification card package) or for additional free referral links when their initial link has been used by three alters returning their test results. Further, each alter in all three arms who returned his result can become a “secondary index” if he is willing to and meets the following criteria: born biologically male, aged 18 years or above, and ever had sex with another man. He can also apply for three packages (refundable 3 USD deposit for each SST package; free of charge for information package) or referral link to distribute to his alters. For all indexes and alters in the study, researchers will provide a 24/7 hotline and online counselling.

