#### Follow-up survey

All indexes will complete a three-month follow-up survey online. The follow-up surveys will collect information of their experience of using the information packages, SST packages or referral link delivery; information on the relationship between the indexes and the alters; reasons of unwillingness to distribute; history of syphilis, HIV and other STIs testing in the past 3 months; and sexual behaviors in the past 3 months. Potential adverse events such as forced alters to test, received physical and/or verbal abuse, or being misunderstood from alters etc. during the delivery procures are asked.

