Several challenges might emerge in the implementation of this study. First, adverse events such as forced testing, physical and verbal abuse among participants, being misunderstood during the delivery procedures may occur. The findings of these questions will provide insights to design better syphilis self-testing support. Second, existing intervention delivery cannot guarantee all three packages or links are distributed. To encourage distribution, indexes will receive 3 USD for each successful distribution. In addition, we will try to understand why indexes fail to distribute any or partial packages via our survey. This information will help to improve current distribution models. Third, we ask for a refundable deposit in the SST arm if indexes wish to apply for SST packages again or secondary indexes wish to apply for SST packages. This might greatly discourage participation. For future studies, we need to discuss whether or not we should keep using this refundable deposit or adjust the amount if recruitment needs to be expanded. Lastly, though we used an objective measure for our primary outcome (photo verified syphilis testing results), there is a possibility that we underestimate the number of alters testing for syphilis if they don’t upload their testing results. We try to mitigate this by offering alters monetary incentives after their testing result is verified by a research assistant.

There are some limitations in this study. First, recruitment takes places in specialist hospitals and local CBOs. This will exclude individuals who are less likely to attend these recruitment sites, leading to sample bias. Second, we use data from treponemal test results, which might overlook testers’ treatment history and clinical data that help differentiate new and old cases.

In conclusion, this study will provide data on optimizing syphilis self-testing programs to increase syphilis testing uptake and earlier syphilis diagnosis among MSM in China.

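### Alters are asked about forced testing and abuse only if they upload a result, so alter-reported harm comes from a group selected by the primary outcome, with almost nobody in the control arm

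*Protocol article*

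**What the plan says.** The protocol article lists among its secondary outcomes "Adverse events during the delivery procedures in each arm". The Secondary analysis section compares the incidence of these events across the three arms by descriptive analysis and a chi-square test.

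The article describes two instruments that ask about them.

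- **Alter survey.** "Each alter in the three arms will receive an online survey link after uploading their syphilis test results". It contains the alter's harm items: "Adverse events will be asked to identify whether the alters were being forced to test, have received physical and/or verbal abuse, or being misunderstood from" the indexes.
- **Follow-up survey.** "All indexes will complete a three-month follow-up survey online". This does not depend on any alter uploading. Its harm items are "Potential adverse events such as forced alters to test, received physical and/or verbal abuse, or being misunderstood from alters etc".

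There is also a passive channel, described for all arms under the Referral link SST delivery arm heading: "For all indexes and alters in the study, researchers will provide a 24/7 hotline and online counselling". It is not described as a means of recording adverse events.

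The Discussion expects that "adverse events such as forced testing, physical and verbal abuse among participants, being misunderstood during the delivery procedures may occur". It also notes that some alters may not upload, but treats this only as an under-count of testing.

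**The concern.** The named harms arise when an index offers a card, kit or link. The alter's account is sought only later, once he has uploaded a result, and an uploaded and verified result is what the primary outcome counts. On the alter side, a safety outcome is thus conditioned on an event that happens after randomisation and that the interventions are designed to change.

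The incentives make this more than a formality. The index earns 3 USD for each alter who returns a result and completes the survey, so pressure on alters is a foreseeable harm. An alter who is pressed or abused and walks away gets no questionnaire. At stake is whether the trial can say anything dependable about harm to alters, and whether the arms can be compared on it. No analysis can recover reports that were never sought.

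**Working it through.** **Step 1. Who is asked what.** Setting the sections side by side:

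| Person | Asked directly about harm? | Other route |
|---|---|---|
| Alter who uploads | Yes (Alter survey) | Index survey, hotline |
| Alter who accepts but does not test or upload | No | Index survey, hotline |
| Alter who refuses | No | Index survey, hotline |
| Index | Yes, at 3 months (Follow-up survey) | Hotline |

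The end-of-study contact in the Follow up section does not fill the gap. It concerns alters with reactive results and no proof of confirmation or treatment, and it asks about linkage to care.

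For alters in the second and third rows, the index survey lists having forced alters to test, and abuse or misunderstanding coming from alters. Abuse done to an alter is not listed, although the list is open-ended. The informant is the person who would have applied the pressure. The Missing data plan expects loss below 20%, and the sample size allows for 20%, which is up to 20 of 100 indexes per arm.

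**Step 2. How many alters would be asked.** The plan gives no figure of its own to reproduce. Inputs:

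- indexes per arm: 10 clusters × 10 = 100 (Sample size);
- initial packages or link uses per index: 3 (Table 1), so 300 per arm;
- pilot alters per index: 0.05, 0.60 and 0.45 (Sample size), assumed here to count alters who returned results.

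Alters sent the survey = 100 × pilot mean. Share of alters reached = pilot mean ÷ packages passed on per index.

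| Arm | Alters asked | Share if all 3 passed on | Share if 1 of 3 passed on (assumption) |
|---|---|---|---|
| Control | 100 × 0.05 = 5 | 5/300 = 1.7% | 5/100 = 5% |
| Standard SST | 100 × 0.60 = 60 | 60/300 = 20% | 60/100 = 60% |
| Link | 100 × 0.45 = 45 | 45/300 = 15% | 45/100 = 45% |

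Overall, with all packages passed on, this is 110/900 = 12%. The number asked differs by 0.60/0.05 = 12 times between standard SST and control. The shares differ by the same factor only if the arms pass on the same number of packages. Additional packages and secondary indexes are ignored. The counts are upper limits on alter reports for these inputs, since not every uploader need complete the survey.

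**Step 3. What those numbers could show.** Suppose a harm has true frequency p among uploaders, all answer, and clustering is ignored. The chance of at least one report is 1 − (1 − p)^n:

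| p | Control, n = 5 | Standard SST, n = 60 | Link, n = 45 |
|---|---|---|---|
| 1% | 5% | 45% | 36% |
| 2% | 10% | 70% | 60% |
| 5% | 23% | 95% | 90% |

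If nobody reports a harm, the one-sided 95% upper limit is 1 − 0.05^(1/n): about 45%, 4.9% and 6.4%. A clean alter-side record in control would say very little.

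**Step 4. Direction.** Two mechanisms pull opposite ways. Abuse that makes an alter refuse removes him from the survey and lowers the observed rate. Pressure that succeeds produces a tester, who may also be pressed to upload because the index's payment depends on it, and this raises the rate among uploaders. The article gives nothing from which to weigh one against the other.

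**The case against.** A reader might infer that harm to non-uploading alters cannot be recorded at all, or that the trial measures harm only among those who complied. The documents do not support either reading. Every index is asked at 3 months, whether or not anyone uploads, and the items cover having forced an alter as well as harm to the index himself. The secondary outcome is not confined to alters, so part of it is sought from all randomised indexes. The hotline is open to everyone.

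A reader might also infer that the harm rate must be biased low because uploaders are willing testers. That does not follow: the first harm listed is being forced to test, and a forced alter may well upload. Nor does a twelvefold difference in the number of uploaders by itself bias a rate among them.

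The 300-package denominator can also be challenged. The Discussion accepts that not all packages will be distributed, and a package never offered cannot cause a delivery harm. The shares are therefore given as a range. Lastly, harm denominators and questionnaire layout may properly sit in an analysis plan or full protocol that is not shown, and their absence is not the point here.

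What survives is the collection rule that the article does state. Alters are asked after upload, no described instrument asks the others, and the index survey is a partial substitute that does not list abuse done to alters.

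**Conclusion.** The concern holds in a limited form. Alter-reported delivery harm is solicited only from alters who upload a result. Harm to the rest can surface only through index self-report or unsolicited contact. About 5, 60 and 45 alters per arm would be asked, between 1.7% and 5% of those offered a package in control, 20% to 60% in standard SST and 15% to 45% in the link arm.

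These figures rest on the pilot means applying to the trial and counting returned results, on between one and three packages per index being passed on equally across arms, and on ignoring additional packages and secondary indexes.

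The alter side of the chi-square comparison would use respondents selected differently by arm, with almost none in control. It could support neither a claim of equal safety nor a claim of difference. A secondary safety outcome is affected; the primary result is not. The change should be made before data collection.

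**What to change.** 1. Add an adverse-event reporting link that needs no uploaded result. Put it on the information card and, in the link arm, on the referral link page. Carry the package or link number where possible, so that a report can be assigned to an arm.
2. In the existing 3-month index survey, ask for each package or link whether it was offered, accepted or refused, and whether any named harm occurred to either party. This adds abuse done to alters and supplies the number actually offered.
3. Make harms per randomised index the main arm comparison, so that the denominator is fixed by randomisation. Report alter-reported and index-reported harms separately with their denominators, because arms with more uploaders have more chances to report. Label the alter-reported rate as uploaders only.

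The cost is a slightly longer online survey, one more link on materials already produced, and some reports that cannot be matched to an index or arm. The remedy is incomplete: an alter who refuses the package never holds the card, and one who never opens the link never sees its page. Both remain reachable only through the index, and the report should state this as a limitation.

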### Follow up

The follow-up survey will be administered 3 months after recruitment for indexes. Each index will receive 4 USD after completing the follow-up survey. Any alters with a reactive self-testing results will be referred to undergo free confirmatory laboratory testing and clinical examination at study clinics or other local designated clinics/hospitals. If the participants are diagnosed with syphilis, we will undertake further follow-up to obtain treatment information. Alters with a reactive result who also return photo verification of confirmatory testing results or treatment proof will receive a further 3 USD. Alters with reactive results who do not return any proof for confirmation testing or treatment will be asked about further linkage to care information at the end of study.

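### The adverse-event outcome covers the delivery step only, so harm after a self-read test result cannot enter the comparison between arms

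*Protocol article*

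**What the plan says.** All references are to the protocol article.

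- **Secondary outcomes.** The only harm outcome is the fourth: "Adverse events during the delivery procedures in each arm".
- **Alter survey.** On timing: "Each alter in the three arms will receive an online survey link after uploading their syphilis test results". On content: "Adverse events will be asked to identify whether the alters were being forced to test, have received physical and/or verbal abuse". The list of items then closes with the period that it covers: "or being misunderstood from indexes etc. during the delivery procedures". No later survey of alters is described.
- **Follow-up survey.** Indexes are asked about "Potential adverse events such as forced alters to test, received physical and/or verbal abuse, or being misunderstood from alters etc", again with reference to delivery. On timing, the Follow up section says: "The follow-up survey will be administered 3 months after recruitment for indexes".
- **Follow up.** Alters with a reactive self-test are referred for free confirmatory testing and examination. "If the participants are diagnosed with syphilis, we will undertake further follow-up to obtain treatment information". Reactive alters who send no proof "will be asked about further linkage to care information at the end of study". Harm is not named as a topic of any of these contacts.
- **Arms and interventions** (end of the referral link arm text). A round-the-clock hotline and online counselling are open to every index and alter.
- **Secondary analysis.** Adverse-event incidence is compared across the three arms, descriptively and by chi-square test.

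**The concern.** The arms differ in how a result is obtained. Control alters are invited to a designated facility. In the two self-testing arms the kit is used at the alter's own hand, and the Background describes self-testing as a process in which the user also interprets the result. Distress after a reactive reading, or conflict after disclosing it, is therefore a plausible harm in those two arms. It arises after delivery, so the outcome as worded excludes it whatever its frequency.

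What is at stake is how the comparison in Secondary analysis will be read. A finding of no excess adverse events with self-testing could be taken as reassurance about self-testing in general, in a trial intended to inform its wider use. It would rest on questions that never covered the period after the result.

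**Working it through.** **Step 1. Can a post-result event reach the outcome?** No figure in the plan needs reproducing here. The sources are taken in turn.

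| Source | Who is asked | When | Period or topic covered |
|---|---|---|---|
| Fourth secondary outcome | – | – | Delivery procedures |
| Alter survey | Alters who upload a result | After upload | Forced testing, abuse, misunderstanding; delivery |
| Follow-up survey | Indexes | 3 months | Mirror-image items; delivery |
| Follow up contacts | Reactive or diagnosed alters | After the result, up to end of study | Confirmation, treatment, linkage to care |
| Hotline and counselling | Anyone who calls | Any time | Support; no stated route into the outcome |

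The first three rows share the delivery limit. The fourth has the right people and timing but a different topic. The fifth is passive. No row collects post-result harm for the outcome. The open-ended wording in the two item lists allows other kinds of event but does not change the period.

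The alter survey already comes after the result. The binding limit is therefore the delivery wording more than the timing of the survey, although events that follow the survey would also need a later contact.

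**Step 2. How many alters are involved?**

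Inputs from Sample size: 10 clusters of 10 indexes per arm, so 100 indexes per arm; pilot means of 0.05, 0.60 and 0.45 alters per index. I take these means as alters returning results and ignore extra packages and secondary indexes.

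- Control: 100 × 0.05 = 5
- Standard SST delivery: 100 × 0.60 = 60
- Referral link: 100 × 0.45 = 45
- Self-testers: 60 + 45 = 105

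The document gives no reactive share for testers. The Background cites a prevalence of 5% or more among MSM in at least 42 countries, which is not a positivity rate for these men. I assume 5–20%.

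- Reactive self-testers: 105 × 0.05 = 5.25 to 105 × 0.20 = 21, so about 5–21
- Reactive control alters: 5 × 0.05 = 0.25 to 5 × 0.20 = 1

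**Step 3. What could added questions show?**

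With zero events among n men asked, the exact one-sided upper 95% bound is 1 − 0.05^(1/n).

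- n = 5: 1 − 0.05^(1/5) = 0.451, about 45%
- n = 21: 1 − 0.05^(1/21) = 0.133, about 13%

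Dividing by all self-testers (rule of three, 3/105 = 2.9%) would be the wrong denominator for harm after a reactive result, because most of the 105 would be non-reactive.

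**The case against.** The strongest reply is that this is a choice of scope, made consistently. The trial compares ways of distributing tests. Coercion and abuse between index and alter are the harms that distribution itself can cause, and the plan asks both sides about them. The Discussion names the same harms. There is no internal contradiction, and that stands.

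Several stronger readings are tempting, and the document does not support them:

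- *That post-result harm is the main added risk of self-testing.* The document does not rank risks, and those it names are forced testing, abuse and being misunderstood. It supports only that men in the self-testing arms read their own result, which makes such harm plausible.
- *That men with a reactive result are left without support.* The hotline, the counselling and the referral for confirmation say otherwise. The point concerns what is recorded, not what care is offered.
- *That a usable comparison between arms is being lost.* With about 5 control testers and at most about one of them reactive, post-result harm could not be compared between arms even if it were asked about.
- *That all harm after a result goes unrecorded.* The article is condensed, and the full questionnaires and safety procedures are not shown.

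The last reply does not remove the point. The delivery limit is written into the outcome itself and repeated in both surveys, so it is a stated rule and not a detail left to a fuller document.

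**Conclusion.** The point holds as a cheap improvement, not as an error that invalidates an analysis. As worded, the fourth secondary outcome cannot contain harm that follows a test result, and the comparison built on it should not be read as a general safety comparison of self-testing with facility testing.

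The gain from a change is descriptive: counts on roughly 5–21 reactive self-testers, against none as planned. That range depends on the pilot means holding, on results in the two self-testing arms coming from self-tests (Data collection also accepts facility results), and on the assumed 5–20% reactive share. The textual conclusion depends on none of these. Alters who never upload a result receive no survey and would remain unseen either way.

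**What to change.** 1. In Secondary outcomes, widen the fourth outcome to harms during delivery and after testing.
2. Add one or two post-result harm questions to the alter survey and to the contacts with reactive alters already planned in Follow up. Use the same wording in all three arms.
3. In Secondary analysis, report delivery harms and post-result harms separately by arm, as counts per randomised index, together with the number of reactive alters asked. Treat the post-result data as descriptive.
4. If the definition is kept, state in Secondary analysis that the comparison covers delivery harms only and supports no conclusion about harm after a result.

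The cost is a wording change and a slightly longer survey and contact. No new visit, staff or procedure is needed, and clinical management is unchanged.
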